#### Randomisation

Following baseline data collection, participants will be randomised to receive either PD_Manager (the intervention) or to be in the control group (symptom diary/no PD_Manager). Randomisation will be 1:1, blocked and by quota within each country and will be conducted using sealed envelopes prepared by an independent statistician. Given the higher incidence for Parkinson’s in men than in women, its increasing prevalence with age and a concern that younger people may be more accepting of technology than older people, the objective is to recruit 40% women and to have one half of each gender be under 70 years of age.

Participants will be informed of their group allocation immediately, and a researcher will provide the PD_Manager devices (intervention group) or the symptom diary (control group) and give full information about how they are to be used over the following 2-week trial period. Blinding of participants, researchers and clinicians will not be possible given the nature of the intervention.

#### Recruitment of clinicians

Volunteers will be sought from amongst clinicians recruiting patients to the study. They will be provided with an information sheet (see Additional file 2) and asked to provide informed consent (see Additional file 2). Baseline information will be gathered using a short questionnaire covering qualifications, current role, number of Parkinson’s patients treated per week and length of time in practice. Participants will also be asked to complete selected items from the Technology Acceptance Model measure [12, 13] and the Global Attitude to Technology question [14].

### PD_Manager mHealth intervention

PD_Manager devices comprise a wristband (Microsoft Band, Microsoft Corporation, Redmond, WA, USA), a pair of sensor insoles (Moticon GmbH, Munich, Germany), a smartphone (Aquaris M and U models, BQ, Madrid, Spain) and a knowledge platform (hosted by Biotronics 3D, London, UK). The devices are unobtrusive. Their wearability, sensitivity and reliability were tested as part of an earlier proof of concept study, as was the cleaning and sterilising process that occurs before devices are transferred between patients [15]. The intervention will be technically supported by the R&D partners involved in developing the devices, apps and knowledge management platform. Researchers will receive training in use of the devices.

Data that will be captured include:Motor symptoms (tremor, abnormal gait pattern, freezing of gait, body bradykinesia and dyskinesia), captured with the sensor insoles, wristband and phone accelerometers and gyroscopes, 24/7Activity data, including time spent on motor exercising, from the wristband, 24/7Speech quality (sound analysis, phonatory deficit) captured during scheduled task with the smartphone microphone (only at the Italian sites)Speech analysis (dysarthria, qualitative analysis of spontaneous speech, mood, intelligibility) through a web platform (only at the Italian sites)Depression, impulsivity and mood, through questionnaires on smart phone apps (as prompted by messages)Cognitive status through a battery of cognitive games on tailored apps.

The PD_Manager platform includes an education section containing videos and animations on symptoms and tips and other relevant information regarding personal care and how to cope with daily life challenges.

The intervention will last 14 days, which is considered sufficient time to monitor fluctuations for the purpose of planning treatments. Data from the PD_Manager devices and apps will be collected. The smartphone automatically transfers data to the cloud, including the data from the wristband (which is connected to the smartphone). Data is stored in the insoles and will be downloaded by the researcher in encrypted form at the end of the 2-week follow-up period and immediately transferred to the cloud. The devices used, body placement and a preview of motor data collected are shown in Fig. 3.

**Fig. 3 Fig3:**
[figure not shown]
Devices used, body placement and preview of motor data collected

### Control group

Participants in the control group will be asked to record motor symptoms and wellbeing over the 2-week trial period. Motor symptoms will be captured using the Hauser diary, a validated instrument that allows the patient to record, in a dedicated form, his or her motor state every 30 min [16]. This diary is the current gold standard to monitor a patient’s symptoms at home, and it is also frequently used in pharmacological clinical trials to assess drug efficacy. The UCB Parkinson’s Well Being Map™ [17] allows patients to record and monitor the wide spectrum of Parkinson’s symptoms, including all those covered by PD_Manager. It is used to assist preparation for consultations with the healthcare team. Data from diaries will be manually entered into the trial database for analysis.

#### Concomitant care

All other usual care for participants will continue during the 2-week trial. The primary care doctors of all people with Parkinson’s will be informed in writing about their patient’s participation in the pilot study and the treatment arm to which they have been allocated.

### Follow-up

Participants in both groups will receive a phone call from the research fellow on day 5 and day 10 to check on progress and answer any questions. They will meet the clinician at the end of the 2-week trial period for a consultation guided by the data that have been collected. The follow-up appointment will be arranged during the baseline meeting, at a time convenient to participants, and will take place in a clinic at the hospital.

In the intervention group, the clinician reviewing each patient will receive reports with relevant information and management suggestions from the PD_Manager software. In the control group, the content of the patient symptom diaries will be reviewed. If data from either PD_Manager or the symptom diary indicate that management changes are required or referrals to other therapists (such as speech and language therapist, dietician, occupational therapist, physiotherapist) would be beneficial, this will be implemented.

### Acceptability outcomes

Assessment of acceptability for patients and carers will be undertaken at the end of the 14-day intervention period immediately after the feedback consultation with the clinician. A private room in the clinic will be identified for this purpose. Views will be collected by interview. Those in the intervention group will be asked about the following: how comfortable the devices were and how easy they were to use (determined with the same wearability and usability questions used in earlier testing of devices [15]; how useful the feedback they received from PD_Manager was; their views on communications with their neurologist regarding the PD_Manager outputs. The usefulness of the education section will also be assessed. A separate questionnaire will be used for participants in the control group to gather their views about the ease, burden and usefulness of the symptom diary. Questionnaires can be obtained from the corresponding author.

Back end data from the PD_Manager system will be provided to the researchers to enable an analysis of compliance with use of the devices by members of the intervention group. These data will be used to indicate how much the patients/carers valued using the devices.

Face-to-face interviews will be conducted with each clinician to explore their views about the relative usability and acceptability of PD_Manager and the symptom diary, and the value they perceive they provided in generating information for clinical decision making. Feedback will be sought by means of a semi-structured interview schedule on perceived usefulness to patients, carers and professionals, and adaptability to usual working schedules. The treating clinicians will be asked to comment on the ease of interpreting the data generated by the devices and the symptom diary and the ease of using this data in changing the treatment and care management of participants, as well as their views on this means of communicating with participants. The interview schedule can be obtained from the corresponding author.

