**Fig. 2 Fig2:**
[figure not shown]
PD_Manager schematic diagram of trial process

**Table 1 Tab1:** Summary of data collection at each stage

Participant group		Data capture at each stage		
	Baseline	During intervention, PD_Manager group from devices	During intervention, control group symptom diaries	Post-intervention, 2 week follow-up
Patient	Age, gender, education, disease duration, disease stage (Hoehn and Yahr score), main symptoms (tremor, bradykinesia, rigidity, dyskinesia), more affected side, UPDRS scores, current medications, comorbidities, views on technology Outcomes: EQ-5D-5L; PDQ-8; NMSS	Motor symptoms (gait, freezing of gait, bradykinesia, hypokinesia, dyskinesia, exercise); non-motor symptoms (cognition, sleep, mood)	All symptom domains captured through the PD_Manager intervention were self reported in a motor diary [16] and a wellbeing map [17] including: on/off; speech; sleep challenges; cognitive issues; activities and physiotherapy	Interviews on acceptability and ease of use of PD_Manager or symptom diary; usefulness of the education section of PD_Manager Outcomes: EQ-5D-5L; PDQ-8 and NMSS Changes in management plan and referrals
Caregiver	Age, gender, education, views on technology	No information is collected from caregivers in the PD_Manager group	No information is collected from clinicians in the symptom diary group	Interviews on acceptability and ease of use of PD_Manager or symptom diary; usefulness of the education section of PD_Manager
	Outcome: Zarit Caregiver Burden Scale (using short version)			Outcome: Zarit Caregiver Burden Scale (using short version)
Clinician	Qualifications, current role, number of Parkinson’s patients/week, length of time in practice, views on technology	No information is collected from clinicians in the PD_Manager group	No information is collected from clinicians in the symptom diary group	Usefulness and value of the information gathered (PD_Manager and symptom diary) for influencing management decisions; changes in management, referrals made

*EQ-5D-5L* EuroQoL-5Dimenions-5Levels, generic health-related quality of life scale [18–20], *PDQ-8* Parkinson’s Disease Questionnaire-8, disease specific measure of health-related quality of life [21, 22], *NMSS* Non-Motor Symptoms Scale [23], *UPDRS* Unified Parkinson’s Disease Rating Scale [11]

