### Analysis

Reporting of results will follow Consolidated Standards of Reporting Trials (CONSORT) extension guidelines for randomised pilot and feasibility studies [25]. Data relating to individual participants will be recorded using unique study identifiers to maintain confidentiality. Research data will be analysed in each country and merged for comparison purposes. Data relating to quantitative variables (baseline characteristics of participants, acceptability and usability outcomes at follow-up) will be entered into Statistical Package for Social Sciences (SPSS) version 24 (IBM SPSS Statistics for Windows, version 24.0, IBM Corporation, Armonk, NY, USA) and analysed with simple frequencies; the intervention and control groups will be compared using appropriate statistical approaches, depending on the nature of the data. In accordance with the pilot nature of the study, the analysis will be non-confirmatory. Data from quality of life and other health outcomes will be inspected for potential use in any future effectiveness trials. Responses to open questions relating to participants’ views will be subject to narrative review. Two independent researchers will read and re-read comments and agree on themes within the data. The information generated by the PD_Manager devices will be analysed by the partners who developed each device.

We expect most participants to complete the trial, since the follow-up lasts only 2 weeks and ends with a consultation with a neurologist, that is in addition to their usual care. However, it is possible that a participant will be unable to complete or may wish to withdraw from the study, in which case their baseline data will be ignored. Another issue is that participants in the intervention group may not use the technology. We will know this from the automatic collection of data, and we will investigate reasons in the follow-up interview. Similarly, participants in the control group may not complete the diary, in which case we will similarly explore their reasons.

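### Ease of use, comfort and burden are asked only after a feedback consultation that differs by arm, so these answers can be coloured by the consultation

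*Protocol article*

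**What the plan says.** The Acceptability outcomes section fixes one moment for the patient and carer interview: it "will be undertaken at the end of the 14-day intervention period immediately after the feedback consultation with the clinician". In that single interview the PD_Manager group is asked "how comfortable the devices were and how easy they were to use", and also about the usefulness of the feedback, communication with the neurologist and the education section. The control group answers a separate questionnaire on the ease, burden and usefulness of the diary.

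The Follow-up section describes the consultation that comes first. For one arm: "In the intervention group, the clinician reviewing each patient will receive reports with relevant information and management suggestions from the PD_Manager software". For the other: "In the control group, the content of the patient symptom diaries will be reviewed". In both arms, changes of management or referrals may follow. The Analysis section adds that follow-up "ends with a consultation with a neurologist, that is in addition to their usual care".

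The same section plans to compare the groups on quantitative data that include acceptability and usability at follow-up, and calls the analysis non-confirmatory. The Randomisation section says that participants, researchers and clinicians cannot be blinded.

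**The concern.** The interview covers two kinds of experience. Wearing the devices or filling in the diary is over when the 14 days end. The usefulness of the feedback and the conversation with the neurologist can be judged only once the consultation has taken place. The plan asks about both at the later moment.

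A person who has just had an extra appointment with a specialist, perhaps with a change of treatment, may look back on two weeks of sensors or half-hourly diary entries more kindly or less kindly than an hour before. The consultation is arm-specific and the respondents know their arm, so such a shift need not be the same in both arms and need not cancel in a comparison.

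These answers are a main product of the pilot. Comfort, acceptability and ease of use are named in its first specific objective. Acceptability and usability also enter the cost-consequences analysis, and the Discussion says that an effectiveness trial may be warranted if feedback is positive. If ratings of the devices carry some of the effect of the consultation, the sponsor learns less about whether the devices themselves need further work.

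**Working it through.** No arithmetic settles this point. It concerns the order and content of assessments, so the check is to set the sections side by side.

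**Step 1. Is there an earlier rating?** Table 1 lists "Interviews on acceptability and ease of use of PD_Manager or symptom diary" only in the post-intervention column, for patients and for carers. The only contacts described during the two weeks are calls: "Participants in both groups will receive a phone call from the research fellow on day 5 and day 10 to check on progress" and to answer questions. No acceptability items are attached to them. The article therefore describes no rating of comfort, ease or burden before the consultation.

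**Step 2. Does the consultation differ by arm?** Yes, by design. The clinician has software reports with suggestions in one arm and diary content in the other.

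**Step 3. Which items are exposed, and how?** From the Acceptability outcomes section:

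| Item | Listed for | Needs the consultation? | What is exposed |
|---|---|---|---|
| Ease of use | both arms, on separate questionnaires | no | between-arm comparison and level in each arm |
| Comfort | PD_Manager only | no | level within that arm |
| Burden | diary only | no | level within that arm |
| Usefulness of feedback; communication with the neurologist | PD_Manager | yes | nothing: the timing is right |
| Usefulness of the diary | control | in large part, as the diary serves the consultation | not counted here |

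The between-arm argument therefore rests on ease of use alone.

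**Step 4. Does anything else in the plan separate the two influences?**

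- *Baseline attitudes to technology and stated preference.* These are measured before randomisation, so they cannot account for an event at day 14.
- *Device compliance data and diary completion.* Both are formed before the consultation and are free of it. They show use, not how easy or comfortable that use was.
- *Management changes and referrals.* Table 1 records them at follow-up, so ease can be tabulated by whether management changed. That split is made on something that happens after randomisation and may itself depend on arm. It also misses general satisfaction with the consultation, and it does not recover a rating given before it.

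**Step 5. Size.** The planned sample is 110 + 50 + 20 + 20 = 200 dyads, 100 of them with PD_Manager, and all are interviewed after the consultation. The article gives no response scale, standard deviation or expected difference for the acceptability items, so a shift cannot be computed. There is only a benchmark for what would be noticeable. With 100 per arm and complete data, the standard error of a difference in means is √(1/100 + 1/100) = 0.14 standard deviations. This describes the precision of the comparison and is not an estimate of the shift.

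**The case against.** The strongest reply is that the consultation belongs to what is being tested. The Background and Design sections present PD_Manager as a way to inform care planning, compared with a diary used for the same purpose, and the report to the clinician is the system's output. Acceptability judged after a full cycle of monitoring and feedback is a legitimate target and close to intended use. This stands for overall acceptability, usefulness and communication, which should stay after the consultation. It does not explain why comfort and ease over the preceding 14 days must wait for it.

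Other points stand in part:

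- The first specific objective is not itself comparative. The comparison with the diary comes from the overall aim and the Analysis section.
- Behavioural measures untouched by the consultation exist in both arms, through device data and diary completion. They complement a rating but do not replace it.
- The pilot is non-confirmatory, with simple frequencies and narrative review, so no error rate is at stake. A descriptive answer can still be shifted.
- The questionnaires are not shown, and their wording may direct respondents to the 14 days. That could reduce the problem but would not change the timing.
- Two sittings add some burden for patients whose symptoms fluctuate.

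A reader might go further and infer that dyads whose treatment changed cannot be distinguished from dyads who found the method easy. Table 1 contradicts this, because management changes are recorded and ease is a separate item. A reader might also infer a spurious between-arm difference in comfort and burden. Each of those is listed for one arm only, so the document does not support that.

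**Conclusion.** The point holds in a limited form. Every patient and carer rating of the monitoring experience is taken just after a consultation whose content differs by arm, and no earlier rating is described. The comparison of ease of use is exposed to a differential shift. The levels of comfort (PD_Manager) and burden (diary) may be shifted within their arms.

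It is tempting to conclude that PD_Manager ratings will be inflated, or to attach a number to the bias. The documents support neither. A disappointing consultation could lower ratings as readily as a good one could raise them, and any figure in standard deviations would only restate its own assumption.

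The conclusion assumes that the article describes the visit in its actual order and that the unseen questionnaires contain no pre-consultation part. The consequence is for interpretation and for the design of the later trial. The change is worth making because it is cheap and bears on the first objective. Ease would still be asked on two different questionnaires to unblinded respondents, and reordering does not cure that.

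**What to change.** Split the interview within the same day-14 visit, in both arms.

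1. **Before the dyad sees the clinician:** comfort or wearability (PD_Manager), ease of use (both arms) and burden (diary).
2. **After the consultation:** usefulness of feedback, communication with the neurologist and overall acceptability.
3. **Reporting:** present the two sets separately and label each by its timing. Do not redefine acceptability as the pre-consultation part alone, since that would change the question.
4. **Descriptive check:** tabulate the post-consultation answers by the management changes and referrals already recorded, and state that this split is made after randomisation.

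The cost is a reordered visit and an edited interview schedule, with two short sittings and a slightly earlier arrival for dyads. No further visit is needed. In the PD_Manager arm the researcher already downloads the insole data at the end of the two weeks, which may offer a slot for the first part. The control arm would need an equivalent moment, for instance when the diary is handed in.

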### Feasibility assessment of effectiveness outcomes

As a test of feasibility, data collection at baseline and follow-up will include potential outcomes that might be used in a subsequent fully powered effectiveness trial. Outcome measures for people with Parkinson’s to be used are:EQ-5D-5L (EuroQoL-5Dimensions-5Levels), a commonly used generic measure of health-related quality of life across five domains (mobility, usual activities, self-care, pain, anxiety/depression), each scored on a 5-point scale (no problem to severe problem/unable) that provides a utility index for use in economic evaluations [18–20]PDQ-8 (Parkinson’s Disease Questionnaire-8), the short form of a Parkinson’s disease-specific measure of health-related quality of life covering eight domains scored on a 5-point scale (never to always/cannot do at all) [21, 22]NMSS (Non-Motor Symptoms Scale) for Parkinson’s, covering severity and frequency of 30 items across nine domains [23]

Live-in carers will be asked to complete the short version of the Zarit Caregiver Burden Scale consisting of 12 items, in two domains: personal strain and role strain. Each question is scored on a 5-point Likert scale (0, never to 4, almost always), giving a range of summed scores 0–48, with higher score representing a higher feeling of being burdened [24].

### Analysis

Reporting of results will follow Consolidated Standards of Reporting Trials (CONSORT) extension guidelines for randomised pilot and feasibility studies [25]. Data relating to individual participants will be recorded using unique study identifiers to maintain confidentiality. Research data will be analysed in each country and merged for comparison purposes. Data relating to quantitative variables (baseline characteristics of participants, acceptability and usability outcomes at follow-up) will be entered into Statistical Package for Social Sciences (SPSS) version 24 (IBM SPSS Statistics for Windows, version 24.0, IBM Corporation, Armonk, NY, USA) and analysed with simple frequencies; the intervention and control groups will be compared using appropriate statistical approaches, depending on the nature of the data. In accordance with the pilot nature of the study, the analysis will be non-confirmatory. Data from quality of life and other health outcomes will be inspected for potential use in any future effectiveness trials. Responses to open questions relating to participants’ views will be subject to narrative review. Two independent researchers will read and re-read comments and agree on themes within the data. The information generated by the PD_Manager devices will be analysed by the partners who developed each device.

We expect most participants to complete the trial, since the follow-up lasts only 2 weeks and ends with a consultation with a neurologist, that is in addition to their usual care. However, it is possible that a participant will be unable to complete or may wish to withdraw from the study, in which case their baseline data will be ignored. Another issue is that participants in the intervention group may not use the technology. We will know this from the automatic collection of data, and we will investigate reasons in the follow-up interview. Similarly, participants in the control group may not complete the diary, in which case we will similarly explore their reasons.

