### Aims and objectives

The aim of the pilot study is to explore the acceptability and utility of the PD_Manager system to patients, carers and clinicians, in a community setting, compared to a symptom diary, to inform further developments and the design of a larger clinical trial which will assess effectiveness (patient and carer health outcomes).

The specific objectives of the pilot study are to:Assess patient perspectives of the PD_Manager mHealth platform regarding comfort, acceptability, ease of use and understanding of Parkinson’sAssess the views of clinicians about the PD_Manager mHealth platform, i.e. usefulness of the information provided for decision making regarding patient management; acceptability in clinical practice; confidence in reliability of the informationExplore the resource implications and costs of the PD_Manager system for patients/carers and providers and consider these in the light of potential outcome differences, compared to the symptom diary, in a cost-consequences framework.

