#### Recruitment, consent and baseline data collection of patient/carer dyads

People with Parkinson’s and their live-in carers will be identified by the consultant neurologist at each centre during routine clinic appointments or following an inpatient episode and invited to take part in the study. Eligibility will be confirmed by the clinician through completion of an eligibility checklist (based on the inclusion and exclusion criteria). The consultant will explain the purpose of the study and provide an information sheet containing full details of the study (see Additional file 2). The dyads will be given time to consider and asked to contact the research team if they want further information or wish to participate. Those who volunteer will be given an appointment to attend the hospital to meet a research nurse, where consent will be taken (separately by the person with Parkinson’s and the carer — see Additional file 2) and baseline data collected (from records, interview and clinical examination). Participants will be given unique study identifiers to maintain anonymity.

Baseline data collected (see Table 1) for the person with Parkinson’s will include disease duration, disease rating — Unified Parkinson’s Disease Rating Scale (UPDRS) score [11], disease stage [10], side of onset, current symptoms (tremor, bradykinesia, rigidity, dyskinesia), more affected side, Parkinson’s medications, comorbidities and body mass index (BMI) calculated from ‘height and weight’. Age, gender, ethnicity, education level and comorbidities will be collected for both members of the dyad. In addition they will both be asked if they have a preference for either the PD_Manager system or the symptom diary and will be questioned regarding their attitudes and expectations for each approach (using the Technology Acceptance Model measure [12, 13] and the Global Attitude to Technology question [14]), as these attitudes may affect the views they will express after the trial.

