The pilot study has been designed to avoid standard risks of bias wherever possible. Participants will be randomised to the intervention and control groups to protect against selection bias, and care has been taken to ensure both groups receive the same attention at all stages of the study. Attrition or non-compliance (with devices or symptom diaries) do not constitute an issue but rather are actions of interest in our analysis of acceptability. However, the nature of the intervention is such that clinicians cannot be blinded to the group allocations. Potential does exist for selective outcome reporting. Hence, we are gathering information on attitudes to technology at baseline from participants, carers and clinicians.

The pilot study will not evaluate effectiveness and cost effectiveness of the PD_Manager system, although such a trial may be warranted if feedback from this pilot is positive. Outcome measures that may be used in an effectiveness trial are being tested within the pilot, and the findings will provide a basis for sample size calculation for a definitive trial. Preliminary cost estimates will also be computed in the pilot study to provide initial indications about the value of gathering further evidence from a larger trial.

Data security and confidentiality are major issues in trials of this sort. Data Protection Directive 95/46/EC, on the protection of individuals with regard to the processing of personal data and on the free movement of such data, will be strictly followed. Data from devices will be transferred (as described earlier) and stored in a web-based cloud database (NoSQL Database -3Dnet) in anonymised and encrypted format as employed by Apple for iPhones (a FiWare cloud-based process). The servers storing the information in the cloud platform are based on Biotronics 3D’s 3DnetMedical platform in the UK in an ISO27001-accredited data centre located in London. They are operated in accordance with the Data Protection Act. No third parties can access data either from the devices or during transmission. Access to the database will be strictly controlled and will only be shared with researchers on the PD_Manager project. Administrators of the web-based cloud database will not have access to data. The full data management policy of the cloud administrators is available from the corresponding author.

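### Ignoring the baseline data of participants who leave conflicts with treating attrition as acceptability evidence and prevents any description of who left

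*Protocol article*

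**What the plan says.** The Analysis section of the protocol article recognises that some participants may be unable to finish or "may wish to withdraw from the study, in which case their baseline data will be ignored". It gives no expected rate, only the remark "We expect most participants to complete the trial".

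Three other parts of the article bear on this rule:

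- The Discussion says of people who leave or do not comply: "Attrition or non-compliance (with devices or symptom diaries) do not constitute an issue but rather are actions of interest in our analysis of acceptability".
- The section on recruitment, consent and baseline data collection explains that preference for one method and attitudes to technology are recorded before the trial "as these attitudes may affect the views they will express after the trial".
- The Acceptability outcomes section sets the only patient and carer assessment of acceptability at one time point: it "will be undertaken at the end of the 14-day intervention period immediately after the feedback consultation with the clinician".

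People who stay in the study but do not use the devices are handled separately. Of them the Analysis section says "we will investigate reasons in the follow-up interview", and it plans the same for incomplete diaries. It states no equivalent step for people who leave.

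**The concern.** The aim is to "explore the acceptability and utility of the PD_Manager system to patients, carers and clinicians", with the symptom diary as comparator. In such a trial, leaving early may itself be a reaction to the devices or the diary, as the Discussion accepts. To learn from it, one needs to know who left: whether they were older, more severely affected, wary of technology, or allocated to the method they had not wanted. The baseline assessment records exactly these things, and the rule sets them aside for the one group in whom they would explain attrition.

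Two further purposes suffer. The sample of 200 is justified partly by a wish to compare men with women and different age groups, and the Randomisation section voices a concern that younger people may accept technology more readily. Under the rule, nobody could examine whether older participants leave more often. The pilot is also meant to inform the sample size of a definitive trial, yet its baseline values of EQ-5D-5L, PDQ-8, NMSS and the short Zarit scale would come only from those who stayed.

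**Working it through.** The plan states no figure on this point. The check is mainly one of consistency, followed by a small illustration.

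**1. Order of events.** The Randomisation section places allocation after baseline data collection. The rule therefore reaches people who have been randomised and whose data already exist.

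**2. What each analysis needs, and whether it survives the rule.**

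- Withdrawals counted by arm, and the retention figure: these need allocation and withdrawal status. Neither is a baseline variable, so they survive.
- Reasons for non-use among people who attend follow-up: these participants keep their baseline data and are interviewed, so this survives.
- Acceptability among completers: this comes from the final interview and is unchanged by the rule.
- Leavers compared with completers on age, gender, severity, preference or attitudes: this needs leavers' baseline data and is lost.
- Baseline table of everyone randomised, and baseline outcome SDs: these need leavers' baseline data and are reduced to completers.

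**3. Other sources on leavers.** The acceptability interview follows the final consultation, which someone who has withdrawn would not be expected to attend. Back-end device data up to withdrawal may exist, but only in the PD_Manager arm. Both arms receive phone calls on days 5 and 10, but the article describes these as progress checks and does not say that reasons for leaving are recorded. Baseline data are therefore the main information on leavers, above all in the diary arm.

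**4. Number of dyads affected.** The total comes from the Participants section: 110 + 50 + 20 + 20 = 200, which agrees with the stated total. The withdrawal rate d is an assumption. Dyads removed from the baseline description = 200 × d:

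- d = 5%: 200 × 0.05 = 10 removed, 190 left
- d = 10%: 200 × 0.10 = 20 removed, 180 left
- d = 20%: 200 × 0.20 = 40 removed, 160 left

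In England or Greece, with 20 each, the same rates remove 1, 2 and 4.

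**5. A related illustration that does not measure this defect.** Suppose a share a of completers find their method acceptable and every leaver counts as non-accepting. The share among all randomised is then a × (1 − d). With a = 80% and d = 5%, 10%, 15% and 20%, this gives 76%, 72%, 68% and 64%. With 80% of completers in both arms but withdrawal of 15% on PD_Manager and 5% on diary, the completer difference is 0 and the all-randomised difference is 0.80 × 0.85 − 0.80 × 0.95 = 0.68 − 0.76 = −8 percentage points. These gaps arise because leavers have no follow-up interview. Retaining their baseline data would leave the 80% unchanged.

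**The case against.** The strongest reply is that the sentence says less than it seems to. It ignores baseline data; it does not say that withdrawals go uncounted or that randomised people disappear from the participant flow. The Analysis section commits to the CONSORT extension for pilot trials, under which counts by arm could be expected. Attrition can therefore be studied to a degree, and the conflict with the Discussion is partial. The article also plans explicitly for people who stop using the devices or diary but attend follow-up. Finally, this is a pilot with a non-confirmatory analysis and a two-week follow-up, so losses may be few.

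All of this stands, and it limits the point. A reader might infer that attrition cannot be compared between arms, that the retention figure would be wrong, or that nobody could describe those who abandoned a method. The article does not support these readings, for the reasons in step 2 of the working.

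A reader might also take the 4 to 16 point gaps (80% against 76% to 64%), or the −8 point contrast, as the bias caused by the rule. They are not. The rates are assumed, and the protocol defines no binary acceptability endpoint common to both arms: the PD_Manager arm answers wearability and usability questions, the diary arm a separate questionnaire. Treating every leaver as non-accepting is also a worst case, because the rule covers people who could not finish for unrelated reasons.

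The reply does not answer the loss of the leavers' profile. That follows from a stated rule, not from a detail left to an analysis plan.

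**Conclusion.** The point holds in limited form. The Analysis section discards already collected baseline data of people who leave, while the Discussion treats leaving as informative and the baseline section explains why attitudes and preference matter. Counts by arm remain possible; a description of who left does not, and the baseline table and baseline SDs would describe completers only. Follow-up SDs are not at issue, since they can come only from people with follow-up.

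The size cannot be derived from the article, which gives neither an attrition nor an acceptability rate. The 10 to 40 dyads lost from the baseline description rest on assumed withdrawal of 5% to 20%; if nearly everyone completes, the loss is small. The judgement that baseline data are the main information on leavers assumes that those who withdraw do not attend the final interview. The matter should be fixed: the rule works against the trial's central aim and is cheap to correct, but the analysis is exploratory and the rest of it is unaffected.

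**What to change.** Replace the sentence in the Analysis section with wording along these lines: All randomised dyads are kept in the baseline table by arm, unless a participant asks for their data to be deleted. Withdrawal is reported by arm, with its timing and any reason volunteered, as an acceptability outcome. Baseline characteristics, preference and technology attitudes of those who withdraw are compared descriptively with those of completers. Acceptability is reported among completers, with the number randomised shown alongside.

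A summary that counts acceptability-related withdrawals as non-accepting may be added, as a sensitivity analysis only. The Analysis section and the Discussion would then agree.

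The cost is one short paragraph and slightly more descriptive analysis. No extra baseline collection is needed; timing and any volunteered reason only have to be noted when someone leaves. The resulting picture of acceptability may be less favourable.
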